### Plans to give access to the full protocol, participant-level data, and statistical code {31c}

The datasets used or analysed, as well as the statistical code, will be made available by the corresponding author upon reasonable request and in consultation with the research team of this study.

### Oversight and monitoring

#### Composition of the coordinating centre and trial steering committee {5d}

The overarching research team consists of the principal investigator, senior researchers, the trial coordinator, and research assistants of de Viersprong. The daily coordination of the trial will be done by the principal investigator and trial coordinator. The trial coordinator and the research assistants are responsible for day-to-day contact with the participants and the therapists at the involved institutions. Each institution has a contact person, with whom the principal investigator and trial coordinator have regular meetings to monitor the progress of the trial at the specific institution. To monitor the overall progress of the trial, the overarching research team will meet every month, or if necessary, more frequently. Participants can consult an independent expert with questions about the trial.

A TSC will be established, consisting of the principal investigator and manager from each treatment location, professors from different universities, and the chair of the Client Council of de Viersprong. This committee can be consulted for advice and monitor the serious adverse events (SAE) during the trial. The TSC will meet two to three times a year, or if necessary, more frequently. The TSC may decide to discontinue or terminate the trial prematurely if there is a significant difference in SAEs (> 5) between the two treatment conditions.

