## Methods: participants, interventions, and outcomes

### Study setting {9}

Three mental healthcare institutions in the Netherlands participate in this study: Mentaal Beter (Bergen op Zoom, Roosendaal, Etten-Leur, and Breda), GGz Breburg (Breda), and de Viersprong (Bergen op Zoom). All three of these institutions provide treatments for young people referred for (emerging) mental health problems and offer interventions for a wide range of mental health problems. GGz Breburg provides both MBT-early and CBT, while Mentaal Beter only provides CBT and de Viersprong solely provides MBT-early. Consequently, adolescents referred to Mentaal Beter and randomized to MBT-early will receive treatment administrated by therapists from de Viersprong, while those referred to de Viersprong and randomized to CBT will be treated at Mentaal Beter.

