#### Concealment mechanism {16b}

Participants are randomized by an independent researcher, following a password-protected computer list with the 1:1 allocation sequence. Allocation will be only revealed to the adolescent, therapist and trial coordinator upon randomization by the independent researcher. The research assistants will not be informed about the allocation.

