#### Implementation {16c}

After informed consent is provided and baseline assessment has taken place, an independent researcher will generate the allocation and inform the trial coordinator about the result. To keep the research assistants blind for the allocation, the trial coordinator directly informs the adolescent (and parents) and therapist about the assigned treatment.

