### Assignment of interventions: blinding

#### Who will be blinded {17a}

Research assistants are kept blind for the treatment allocation. The trial coordinator, adolescent (and parents), and therapist will not be blinded but are strongly inculcated to not disclose the assigned treatment during end-of-treatment assessment and follow-up assessments. To check whether research assistants are still blinded for the assigned treatment during the study, research assistants are asked after each assessment to which treatment the adolescents was allocated.

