### Data collection and management

#### Plans for assessment and collection of outcomes {18a}

To assess the primary outcome, semi-structured interviews will be administered by trained research assistants at baseline, end of treatment and at 24-month follow-up. To assess the secondary outcomes, questionnaires will be collected through the online database BergOp (https://www.bergop.info), to minimize data entry errors. For a detailed description of the instruments used in this trial, see the ‘Outcomes {12}’ section. For the administration of the BPDSI-IV-ado and C-SSRS, research assistants will be trained and supervised by senior researchers. The research assistant writes a report on the results of the BPDSI-IV-ado and, if requested, provides this report to the adolescent.

All data will be anonymized and saved in a folder on a secured server of ‘de Viersprong’, which can only be accessed by the research team. The data will be stored, coded, and cleaned before analyses (e.g. checking for duplicates, coding of missings and date of entry) in SPSS.

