#### Adverse event reporting and harms {22}

Adverse events (AEs) are defined as any undesirable experience occurring to a subject during the study, whether or not considered related to the trial procedure. Adverse events, including self-harm or family crises, are considered to be related to the nature of the mental problems of these adolescents/families and will be managed by the therapist as part of the regular treatment. The therapist will discuss these adverse events with the adolescent. Reporting for research purposes will only occur in case of an SAE.

The following SAEs will be monitored, recorded, and reported:Lethal suicide attempts or suicide attempts that require hospitalizationAny other behaviour that may be related to the patients’ presenting problems that requires inpatient hospitalization or that may result in persistent or significant disability/incapacity (e.g. very serious self-harm, overdose)

An elective hospital admission will not be considered as a serious adverse event.

All SAEs occurring from the time of written consent until 90 days after cessation of the trial treatment will be recorded in the case report form.

For each SAE, the following information will be collected:Full details in medical terms and case descriptionEvent duration (start and end dates, if applicable)Action takenOutcomeSeriousness criteriaCausality (i.e. relatedness to trial intervention/investigation), in the opinion of the investigatorWhether the event would be considered expected or unexpected

Events will be followed up until the event has been resolved or a final outcome has been reached.

The research assistant will report all SAEs to the trial coordinator and principal investigator without undue delay after obtaining knowledge of the events, within one working day. The principal investigator informs the trial steering committee in case of a SAE.

The trial coordinator will also report the SAEs through the web portal *ToetsingOnline* to the accredited Medical Ethical Committee that approved the protocol, within seven working days of first knowledge for SAEs that result in death or are life-threatening followed by a period of a maximum of 8 days to complete the initial preliminary report. All other SAEs will be reported within a period of a maximum of 15 days after the trial coordinator has first knowledge of the SAE.

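### The blinded raters of the primary outcome are also given day-to-day contact with therapists, most of whose institutions deliver only one arm, so the blind is put at avoidable risk

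*Protocol article*

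**What the plan says.** All references are to the protocol article.

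- **Who rates.** For the primary outcome, section {18a} states that "semi-structured interviews will be administered by trained research assistants at baseline, end of treatment and at 24-month follow-up".
- **Who is blind.** Section {17a}: "Research assistants are kept blind for the treatment allocation". Section {16b}: "The research assistants will not be informed about the allocation". Section {17b} adds that nobody else in the trial is blinded.
- **How the blind is protected.** Section {16c}: "To keep the research assistants blind for the allocation, the trial coordinator directly informs the adolescent (and parents) and therapist about the assigned treatment". Section {17a} adds two safeguards. The coordinator, families and therapists are told firmly not to reveal the treatment at the end-of-treatment and follow-up assessments, and assistants record a guess of the arm after each assessment.
- **What else the assistants do.** Section {5d}: "The trial coordinator and the research assistants are responsible for day-to-day contact with the participants and the therapists at the involved institutions". Section {22}: "The research assistant will report all SAEs to the trial coordinator and principal investigator without undue delay after obtaining knowledge of the events".
- **Who delivers what.** Section {9} says that "Mentaal Beter only provides CBT and de Viersprong solely provides MBT-early", while GGz Breburg delivers both. Adolescents referred to a one-treatment institution and randomized to the other arm are treated by the other institution's therapists.

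**The concern.** Sections {16b}, {16c} and {17a} keep allocation news away from the assistants. Section {5d} then gives the same staff a standing duty to deal with the people who hold that news. In many trials the identity of a therapist says little about the arm. Here, for two of the three institutions, it settles the arm without anyone having to disclose anything.

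The stake is the primary comparison. Participants, parents and therapists are all unblinded, so the rater's blindness is the main protection against assessment bias on a semi-structured interview that calls for judgement in scoring. Section {5d} places the assistants at de Viersprong, and the description of MBT-early says that the treatment was developed there. That makes a credible blind more important to readers of the result.

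**Working it through.** No figure in the protocol bears on this point, so the check is a comparison of sections.

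1. **Are the raters and the contact persons the same staff?** Sections {16b}, {16c}, {17a}, {18a}, {5d} and {22} all speak of the research assistants without distinction. None separates those who rate from those who deal with therapists.

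2. **Is the therapist contact limited in time?** Section {5d} sets no limit. Contact during screening and consent would be harmless because it precedes allocation, but the text does not stop there.

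3. **Does knowing the therapist reveal the arm?** From section {9}:

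| Therapist's institution | Treatments delivered | What an assistant can infer |
|---|---|---|
| Mentaal Beter | CBT only | CBT |
| de Viersprong | MBT-early only | MBT-early |
| GGz Breburg | both | not settled by institution |

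   Two of three institutions therefore identify the arm. The link runs through the therapist's institution and not strictly through the building: section {9} does not say where a Mentaal Beter referral randomized to MBT-early is seen, only that de Viersprong therapists give the treatment. At GGz Breburg, section {11c} speaks of CBT teams and MBT-early teams, so the therapist's name may also point to the arm, but the text does not establish this.

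4. **Which ratings are exposed?** Table 1 places the interview at baseline, end of treatment and 24 months. Baseline precedes randomization. The end-of-treatment rating, which fixes the primary effect, and the 24-month rating do not. The C-SSRS interview follows the same schedule.

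5. **Do the safeguards close the gap?** The non-disclosure instruction covers the assessments after randomization. It does not cover day-to-day contact between them, and it cannot hide which institution a therapist belongs to. The guess check measures unblinding after it has happened.

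6. **Does SAE reporting add to it?** Section {22} covers consent until 90 days after trial treatment stops, so the end-of-treatment rating can follow an SAE. The record includes action taken and relatedness to the intervention. The route is narrow: it touches only participants with an SAE, the investigator judges causality, and an assistant may learn of an event from the adolescent at an interview without learning the arm.

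**The case against.** The strongest reply is that the sections can be read together. Section {5d} shares the duty between coordinator and assistants. Elsewhere the assistants deal with families, in screening, consent and motivation for assessments, and the coordinator deals with therapists about allocation. On that reading no assistant ever needs to contact a given participant's therapist after randomization. The non-disclosure instruction also applies at the very visits where the outcome is rated. And this is a condensed article, so a finer division of duties may stand in the full protocol.

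Much of this stands. A reader might infer that the two sets of duties cannot both hold, or that routine contact does reveal the allocation. The documents do not support either: {5d} does not say that contact after randomization is made participant by participant, and unblinding is an inference from the institution, not a stated fact. The SAE route is a minor addition. By 24 months the link is looser still, because section {30} allows the non-assigned treatment after dropout or completion.

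What the reply does not remove is the wording of {5d} itself. The point is not that something is missing: the article gives blinded raters a duty that undermines their blinding, and no section restricts it. If practice already follows the compatible reading, the text should say so.

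**Conclusion.** The point holds as a risk to the blind that the plan creates and could avoid. As written, {5d} lets the raters of the primary outcome have therapist contact after randomization. At two of three institutions, knowing the therapist is enough to infer the arm; at GGz Breburg it is less certain. The safeguards in {17a} reduce the risk but do not cover this contact.

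The conclusion assumes that assistants act on {5d} after randomization and that the contact lets them link a therapist to a participant. The documents confirm neither.

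A reader might go on to put a figure on the bias, as a share of the planned effect of d = 0.50, or to conclude that it favours MBT-early. The protocol gives no referral shares by institution, no rate of unblinding and no effect of unblinding on BPDSI-IV-ado ratings, so neither the size nor the direction can be derived.

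**What to change.** 1. In {5d}, state that after randomization all contact with therapists and treatment teams goes through the trial coordinator, who already knows the allocation, and that research assistants are limited to assessment contacts with participants and parents.
2. In {17a}, extend the non-disclosure instruction from the assessments to every contact with research assistants.
3. In {22}, have therapists report SAEs directly to the coordinator, with assistants only passing on events that they learn of during an assessment.

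This needs changes of wording and some more work for the coordinator. It needs no new participants, measurements or staff, and it leaves treatment and the analysis unchanged.

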#### Composition of the data monitoring committee, its role, and reporting structure {21a}

N/A. A data safety monitoring board (DSMB) is not applicable for this trial, due to its relatively small size and the fact that the treatments being investigated are not experimental. However, as mentioned in the ‘Composition of the coordinating centre and trial steering committee {5d}’ section, a TSC will be established, which can be consulted for advice and monitor the SAEs during the trial.

#### Adverse event reporting and harms {22}

Adverse events (AEs) are defined as any undesirable experience occurring to a subject during the study, whether or not considered related to the trial procedure. Adverse events, including self-harm or family crises, are considered to be related to the nature of the mental problems of these adolescents/families and will be managed by the therapist as part of the regular treatment. The therapist will discuss these adverse events with the adolescent. Reporting for research purposes will only occur in case of an SAE.

The following SAEs will be monitored, recorded, and reported:Lethal suicide attempts or suicide attempts that require hospitalizationAny other behaviour that may be related to the patients’ presenting problems that requires inpatient hospitalization or that may result in persistent or significant disability/incapacity (e.g. very serious self-harm, overdose)

An elective hospital admission will not be considered as a serious adverse event.

All SAEs occurring from the time of written consent until 90 days after cessation of the trial treatment will be recorded in the case report form.

For each SAE, the following information will be collected:Full details in medical terms and case descriptionEvent duration (start and end dates, if applicable)Action takenOutcomeSeriousness criteriaCausality (i.e. relatedness to trial intervention/investigation), in the opinion of the investigatorWhether the event would be considered expected or unexpected

Events will be followed up until the event has been resolved or a final outcome has been reached.

The research assistant will report all SAEs to the trial coordinator and principal investigator without undue delay after obtaining knowledge of the events, within one working day. The principal investigator informs the trial steering committee in case of a SAE.

The trial coordinator will also report the SAEs through the web portal *ToetsingOnline* to the accredited Medical Ethical Committee that approved the protocol, within seven working days of first knowledge for SAEs that result in death or are life-threatening followed by a period of a maximum of 8 days to complete the initial preliminary report. All other SAEs will be reported within a period of a maximum of 15 days after the trial coordinator has first knowledge of the SAE.

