##### Criteria for discontinuing or modifying allocated interventions {11b}

Adolescents can withdraw from the study at any time for any reason if they wish to do so without any consequences for their treatment, i.e. they can complete their current assigned treatment (either MBT-early or CBT), but will not be contacted for further assessments. Previously collected data will be included in the analyses.

The research team will register and follow up all potential serious adverse events (SAEs) that might be associated with the treatment (e.g. suicide), which may ultimately lead to the ending of the study. These SAEs will also be reported and discussed at a trial steering committee (TSC). The TSC may decide to end the study prematurely if a significant difference in SAEs (> 5) is shown between the two treatment conditions. For more details on the SAEs, see ‘Adverse event reporting and harms {22}’ section.

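### The recorded-SAE list does not admit events for being fatal or life-threatening, although the reporting clock in the same section uses those two criteria, so some grave events would go unrecorded

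*Protocol article*

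**What the plan says.** The section on adverse event reporting and harms {22} begins with a broad definition of an adverse event: "any undesirable experience occurring to a subject during the study, whether or not considered related to the trial procedure". It then restricts what enters the research record: "Reporting for research purposes will only occur in case of an SAE".

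Two items make up the SAEs to be monitored, recorded and reported:

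- Item 1: "Lethal suicide attempts or suicide attempts that require" hospitalization.
- Item 2: any other behaviour, possibly related to the presenting problems, "that requires inpatient hospitalization or that may result in persistent or significant disability/incapacity (e.g. very serious self-harm, overdose").

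Elective admissions are excluded. Recording runs from written consent to 90 days after the trial treatment ends. Later in the section, the faster of two ethics-committee timelines applies "within seven working days of first knowledge for SAEs that result in death or are life-threatening". All other SAEs have a maximum of 15 days.

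SAE counts have a stated use. Under {5d} the TSC may terminate the trial "if there is a significant difference in SAEs (> 5) between the two treatment conditions", and {11b} repeats the rule. Section {11b} also describes what is followed: "The research team will register and follow up all potential serious adverse events (SAEs) that might be associated with the treatment (e.g. suicide").

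**The concern.** The section uses two sets of seriousness criteria that do not match. Events enter the record through a lethal suicide attempt, hospitalization or possible lasting disability. Once entered, they are sorted for reporting speed by death and threat to life. An event can therefore meet a criterion that the clock treats as most urgent and still never be admitted to the record.

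Because the article reports only SAEs for research, such an event would not be downgraded to a lesser category. It would be left to the therapist as part of regular care.

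The loss would affect three things: the description of harms by arm, the ethics committee's view of the trial, and the SAE difference that is the article's only numerical criterion for stopping early. The article plans no data safety monitoring board {21a} and no interim analysis {21b}, so the SAE record carries considerable weight in a trial of 132 adolescents with depression or anxiety and borderline features.

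**Working it through.** No planned figure is at issue. The check takes types of event through the text of {22}, in three steps: does item 1 admit it, does item 2 admit it, and if neither does, is it recorded anywhere as an event?

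| Event | Item 1 | Item 2 | Recorded as SAE | Meets the fast-clock criterion |
|---|---|---|---|---|
| Lethal suicide attempt | yes | not needed | yes | yes |
| Non-fatal attempt, hospitalized | yes | not needed | yes | if life-threatening |
| Very serious self-harm or overdose, admitted or possibly disabling | no, unless a suicide attempt | yes | yes | if fatal or life-threatening |
| Life-threatening suicide attempt, not hospitalized | no: neither lethal nor hospitalized | no: covers only other behaviour | **no** | yes |
| Death from an accident or medical cause | no | no: not behaviour related to the presenting problems | **no** | yes |
| Other life-threatening event that is not such behaviour | no | no | **no** | yes |

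The last three rows are the gap. In each, the final two columns disagree.

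The fourth row does not depend only on the word *other* in item 2. If item 2 were read generously to include suicide attempts, it would still require inpatient admission or possible persistent or significant disability. A life-threatening attempt with neither would remain outside.

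Next, does any other part of the article close the gap?

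- **{11b}** speaks of all potential SAEs that might be associated with treatment. It adds no criterion for what makes an event serious.
- **{5d} and {21a}** say that the TSC monitors SAEs. They do not define them.
- **The C-SSRS** (Outcomes {12} and Table 1) is a screener of 3–6 yes/no questions given at baseline, end of treatment and 24 months. It may register that suicidal behaviour occurred. It is not described as feeding SAE reporting, and it cannot record a death.
- **The adapted TiC-P** (Economic evaluation) asks parents about the frequency and duration of suicidal crises, but the item is tied to hospitalization, which is the same gate as item 1.

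None of these brings the last three rows into the SAE record.

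On size, a difference of more than 5 means at least 6 events. With the target of 66 per arm, 6 events in 6 different participants would be 6/66 = 9.1% of one arm. Each unrecorded event changes the recorded difference by one. The article gives no expected rate of deaths or of non-hospitalized life-threatening attempts, so how often this would happen cannot be calculated.

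**The case against.** The strongest reply is that the text does not contradict itself. The clock is a timing tier for events already classed as SAEs, and listed events can fill it: a lethal attempt is a death, and a hospitalized attempt may be life-threatening. This is correct. A reader might infer a contradiction, but the text shows only a mismatch between entry criteria and reporting criteria. The mismatch is enough to lose events.

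A second reply is that this is a condensed article. Each SAE record is to state its seriousness criteria, which hints at a fuller set in the complete protocol. That is possible and cannot be checked here. But the article is not silent on the matter: it prints a list and limits research reporting to SAEs. The objection is to what is stated.

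Third, item 2 is wider than it first appears. It covers behaviour that *may* result in disability and gives very serious self-harm and overdose as examples. A reader might infer that every death other than suicide escapes the list. That goes too far, since an overdose fits item 2 naturally.

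Three further inferences are tempting and unsupported:

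- **Bias between arms.** Mentaal Beter gives only CBT and de Viersprong only MBT-early, so one might argue that admission practice makes the same act count in one arm and not in the other. GGz Breburg gives both treatments, and nothing in the article says that the therapy provider decides admission or that practice differs.
- **SAEs as the only harms comparison.** The C-SSRS is a secondary outcome analysed between arms, so suicidality is also compared that way.
- **SAEs as the TSC's only input.** The stopping rule is discretionary, and {5d} lets the committee be consulted for advice. Nothing limits what it may consider.

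**Conclusion.** The concern holds as a gap in the stated recording rule. On a literal reading of {22}, three kinds of event are not recorded as SAEs: a death that does not arise from listed behaviour, a life-threatening suicide attempt without hospitalization, and a life-threatening event that is not listed behaviour. The first two are the clearest. All three meet criteria that the same section uses for its fastest reporting.

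The conclusion rests on two assumptions: that the printed list is the working definition used by those who record events, and that the full protocol does not widen it. It needs no assumption about event rates or admission practice.

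The number of events affected is unknown and may be small. The documents do not show that the gap would decide the stopping rule or distort the comparison of arms, and neither is claimed. It is worth correcting because the events concerned are among the gravest the trial could see and the repair is inexpensive. It does not threaten the primary efficacy analysis.

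**What to change.** Reconcile the SAE list in {22} with the reporting clock in the same section. Add to the recorded SAEs death from any cause and any life-threatening event, including a suicide attempt, whether or not the participant is admitted. The criteria that admit an event would then include those that set its reporting speed, and {11b} and {5d} should point to this single definition. If the full protocol already contains such a definition, it is enough to state it in place of the current list.

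A separate count by arm of suicide attempts without admission would be a useful option but is not needed to close the gap.

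The change concerns recording only and leaves clinical management untouched. It costs a wording amendment, one more category on the existing case report form and slightly more event reporting. As recruitment began in August 2021, the amendment should say whether events since then will be reviewed against the widened list, so that counts use the same definition throughout.
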